## Abstract

**Background:**

The use of ***mother’s own breast milk*** during initial hospitalization has a positive impact not only in reducing potential serious neonatal morbidities but also contribute to improvements in neurodevelopmental outcomes. Mothers of very preterm infants struggle to maintain a supply of breast milk during their infants’ prolonged hospitalization. Galactogogues are medications that induce lactation by exerting its effects through oxytocin or prolactin enhancement. Domperidone is a potent dopamine D_2_ receptor antagonist which stimulates the release of prolactin. Small trials have established its ability in enhancing breast milk production. EMPOWER was designed to determine the safety and efficacy of domperidone in mothers experiencing an inadequate milk supply.

**Methods/design:**

EMPOWER is a multicenter, double masked, randomized controlled phase-II trial to evaluate the safety and effectiveness of domperidone in those mothers identified as having difficulty in breast milk production. Eligible mothers will be randomized to one of two allocated groups: **Group A**: domperidone 10 mg orally three times daily for 28 days; and **Group B**: identical placebo 10 mg orally three times daily for 14 days followed by domperidone 10 mg orally three times daily for 14 days. The primary outcome will be determined at the completion of the **first 2-week period**; the second 2-week period will facilitate answering the secondary questions regarding timing and duration of treatment. To detect an estimated 30% change between the two groups (from 40% to 28%, corresponding to an odds ratio of 0.6), a total sample size of 488 mothers would be required at 80% power and alpha = 0.05. To account for a 15% dropout, this number is increased to 560 (280 per group). The duration of the trial is expected to be 36–40 months.

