### Design

EMPOWER is a multi-centre, double-masked, randomized controlled trial in which 560 mothers will randomized to one of two allocated groups: **Group A**: domperidone 10 mg orally three times daily for 28 days; and **Group B**: identical placebo 10 mg orally three times daily for 14 days followed by domperidone 10 mg orally three times daily for 14 days. (Figure
1) The primary outcome will be determined at the completion of the **first 2-week period** comparing study drug and placebo; the second 2-week period will facilitate answering the secondary questions regarding timing and duration of treatment. The mothers will be contacted when their infants are term gestation (40 weeks post conceptual age) and 6 weeks corrected (6 weeks post date of confinement) to document the feeding patterns (breastfeeding/bottle feeding), continued frequency of breast stimulation, additional use of a galactogogue or alternative after the study period, and the use of supplementation other than mother’s own milk for their infants at these time points. In addition, the mothers will be asked to a few questions regarding the intervention and their participation in the trial.

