### Randomization

Upon consent, the site co-ordinator will be able to randomize the mother using a 24 hour/day web-based randomization service at the data coordinating centre (DCC) at the Centre for Mother, Infant, and Child Research (CMICR) in Toronto. A treatment number will be issued which will correspond to the study medication at the centre which has been previously sent to the site. The study allocation will be randomly assigned in a 1:1 ratio in blocks of 4 and 8. The study participants will be stratified by centre, gestational age groupings (23–26 and 27–29 weeks gestation at delivery) and days post delivery (7–14 and 15–21 days post delivery).

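### 560 randomized mothers allow for about 13% dropout on the required 488, not the stated 15%: a minor arithmetic error worth about one point of power

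*Protocol article*

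**What the plan says.** The sample-size statement is in the abstract of the Protocol article, under Methods/design. The planning effect is given as "To detect an estimated 30% change between the two groups (from 40% to 28%, corresponding to an odds ratio of 0.6"). On that basis "a total sample size of 488 mothers would be required at 80% power and alpha = 0.05". The next sentence adds the allowance for loss: "To account for a 15% dropout, this number is increased to 560 (280 per group").

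In the body, the Design section repeats the total: "560 mothers will randomized to one of two allocated groups". The Randomization section gives equal allocation: "The study allocation will be randomly assigned in a 1:1 ratio in blocks of 4 and 8".

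On timing, the abstract says "The primary outcome will be determined at the completion of the" first two-week period. Study medication runs for 28 days (Duration of study period), and mothers are contacted again at term and at 6 weeks corrected age (Design). No section says over which of these periods the 15% is expected.

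**The concern.** A dropout allowance should leave the required number of evaluable participants once the stated fraction of those randomized has been lost. The article prints all three figures needed to check this: 488 required, 15% lost, 560 randomized. Taking 15% off 560 does not leave 488. The pattern is a familiar one: the required number was apparently multiplied by 1 + d when it should have been divided by 1 − d, where d is the dropout fraction. That applies the 15% to the evaluable mothers, whereas dropout acts on the randomized mothers.

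What is at stake is modest. The stated allowance is the figure against which readers and those overseeing the trial would judge actual attrition. As printed, it tells them that a 15% loss still leaves the number needed for 80% power, when the margin ends earlier. The 488 has almost no slack, so any loss beyond that margin takes power slightly under the stated level.

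**Working it through.** **Inputs, all from the Protocol article.** Rates 40% and 28%, power 80%, alpha 0.05, 488 required, 15% dropout, 560 randomized as 280 per group (abstract, Methods/design); 1:1 allocation (Randomization). The article does not state the sidedness of the test. I take it as two-sided because that reproduces 488; one-sided gives 384.

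**Step 1. Reproduce the 488.** For two proportions with pooled variance under the null and no continuity correction, the number per group is

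n = [z(0.975) × √(2p̄(1 − p̄)) + z(0.80) × √(p₁(1 − p₁) + p₂(1 − p₂))]² / (p₁ − p₂)²

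with p₁ = 0.40, p₂ = 0.28 and p̄ = 0.34.

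- First term: 1.960 × √0.4488 = 1.3130
- Second term: 0.8416 × √0.4416 = 0.5593
- n = (1.8723)² / 0.0144 = 243.4, rounded up to 244 per group, or 488 in total

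This matches the plan exactly. Other standard variants do not: about 482 with unpooled variance, about 486 with the arcsine method, 520 with continuity correction.

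**Step 2. Check the inflation.**

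| Calculation | Result |
|---|---|
| 488 / (1 − 0.15) | 574.1, so 575, or 576 in equal groups (288 each) |
| 488 × (1 + 0.15) | 561.2 |
| Stated in the plan | 560 |

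The stated 560 is the second line rounded down. It is 16 mothers below 576.

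**Step 3. What 560 leaves.**

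- After 15% loss: 560 × 0.85 = 476, or 238 per group; 488 − 476 = 12 short
- Largest loss that still keeps 488: 1 − 488/560 = 72/560 = 12.9%

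**Step 4. What this does to power.** Power is Φ{[|p₁ − p₂| × √n − z(0.975) × √(2p̄(1 − p̄))] / √(p₁(1 − p₁) + p₂(1 − p₂))}.

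- At 238 per group: (0.12 × √238 − 1.3130) / 0.6645 = (1.8513 − 1.3130) / 0.6645 = 0.810, so power is 79.1%
- At 244 per group: (1.8745 − 1.3130) / 0.6645 = 0.845, so power is 80.1%

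Exact enumeration of the uncorrected chi-square test gives 79.0% at 238 per group and 80.3% at 244 per group. With no loss at all (280 per group), the normal approximation gives 85.2%.

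**The case against.** The strongest case on the other side has four parts.

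1. **The effect is very small.** About one point of power and 16 mothers in 576 (2.8%) are at issue. The planning rates are themselves estimates, and a modest error in either could move power by more than this. This stands, and it is why the point is minor.

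2. **A shortfall requires the whole 15% to be missing at day 14.** The primary outcome is measured at two weeks, while medication runs to four weeks and contact continues to 6 weeks post term. If the 15% covers the whole study, mothers lost after day 14 still contribute to the primary analysis, and 488 are kept as long as loss by then is at most 12.9%. The Statistical analysis section also says that regression models will use likelihood-based methods to account for missing data. Those would not recover every missing binary outcome, but the plan does not simply equate dropout with exclusion. This stands as a limit on the consequence. It does not make the printed figures agree.

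3. **Multiplying by 1 + d is a common shorthand, and the sentence does not promise that exactly 488 will remain.** This carries little weight. The sentence says the increase accounts for a 15% dropout from a number just described as required, and it does not do so.

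4. **The article is a condensed source.** The full sample-size section is not shown and might explain the time window or the rounding. It could clarify what the 15% means, but it cannot make 85% of 560 equal 488.

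A reader might infer two stronger conclusions. One is that the trial fails its power target. The documents do not support this, because it depends on a worst-case timing of dropout that they do not state, and even then the loss is about one point. The other is that the error adds to the oddity in the preceding sentence, where the planning rate falls from 40% to 28% although the outcome is an increase in milk volume. It does not: a two-sided comparison of 40% and 28% needs the same number and has the same power whichever group has the higher rate.

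**Conclusion.** The point holds as a minor arithmetic error in a stated sample-size allowance. A total of 560 covers a loss of at most 12.9% on 488, not 15%. At a full 15% loss, 476 mothers remain and power is about 79.1%, against the stated 80%. There is no material loss of power, and no case for enrolling more mothers on this ground.

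The 476 and the 12.9% follow from the printed figures alone. The 79.1% rests on three assumptions: a two-sided test (not stated, but it reproduces 488), loss split equally between the groups, and every dropout missing from the day-14 primary outcome, which is the worst case.

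**What to change.** Keep 560 and correct the dropout sentence in one of two ways:

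- state that 560 mothers (280 per group) allow for about 13% dropout while keeping 488; or
- state that with 15% dropout, 476 evaluable mothers give about 79% power.

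The cost is one sentence and a slightly less favourable figure. The Design section's total of 560 stays as it is, and neither recruitment nor analysis changes.

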**Discussion:**

The use of a galactogogue often becomes the measure of choice for mothers in the presence of insufficient breast milk production, particularly when the other techniques are unsuccessful. EMPOWER is designed to provide valuable information in guiding the practices for this high-risk group of infants and mothers. The results of this trial will also inform both mothers and clinicians about the choices available to increase and maintain sufficient breast milk.

**Trial registration:**

Clinical Trials.gov Identifier: NCT01512225

## Background

Despite the recent perinatal and neonatal technological advances, at least 8.2% of births in Canada are preterm (<37 weeks gestation), a figure that has continued to rise
[1,2]. The very preterm infant is often growth restricted because of the concurrent illnesses and difficulties in optimizing energy and nutrient intake for normal growth
[3]. Studies have suggested that early nutritional intervention (breast milk and preterm formula) that will support growth, in particular brain growth, will lead to an improved outcome even in the presence of injury
[4-6]. There is further evidence to suggest that the use of ***mother’s own breast milk*** compared to infant formula during initial hospitalization has a positive impact not only in reducing potential serious neonatal morbidities but also contribute to improvements in neurodevelopmental outcomes
[6-12]. There is a growing movement in neonatal care for very preterm infants to receive breast milk as the primary source of nutrition rather than rely on preterm formula. Mothers are therefore encouraged to begin pumping their breasts to provide breast milk for their infants. With preterm infants requiring hospitalization for anywhere from 10–16 weeks before their discharge from initial hospitalization, continued and sustained breast milk volume can prove to be a challenge to even the most dedicated of mothers. Most mothers of very preterm infants, for a variety of reasons such as illness, stress and other factors related to preterm birth, are unable to express sufficient amounts of milk to exclusively feed their infants
[11-15].

There have been many identified and studied non-pharmacological measures such as emotional support, kangaroo care, skin-to-skin contact, expressing breast milk at the infant’s bedside, increasing pumping frequency and duration and types of mechanical expression that have been found to contribute to variable levels of success in augmenting the breast milk production in mothers of preterm infants
[16]. For those mothers in whom milk production has declined and is not responding to non-pharmacologic measures, the use of galactogogues is often considered. Galactogogues are medications that induce lactation generally from exerting its effects through oxytocin or prolactin enhancement
[17]. The primary galactogogues used today for prolactin enhancement are dopamine antagonists with the most widely studied being metoclopramide and domperidone. Domperidone is a potent dopamine D_2_ receptor antagonist and was developed and marketed as a prokinetic and antiemetic agent. By blocking dopamine D_2_ receptors in the anterior pituitary, domperidone stimulates the release of prolactin Table
1[18-23].

**Table 1 T1:** Outlines the series of small trials that have evaluated the efficacy of domperidone in mothers of preterm infants

**Study Domperidone**	**N**	**Placebo**	**Randomization**	**Intervention**	**Findings**
De Leo [18]	15	Y	N	10 mg TID 4d	↑ lactation
Petraglia [19]	17	Y	N	10 mg TID 10d	↑ PRL, BM
da Silva [20]	20	Y	Y	10 mg TID 7d	↑ PRL, BM
Campbell-Yeo [21]	46	Y	Y	10 mg TID 14d	↑↑ PRL, BM
Ingram [22]	80	Metoclopromide	Y	10 mg TID 10d	↑ BM
Knoppert [23]	15	N	Y	10 mg vs. 20 mg TID 4 weeks	↑ BM

### Rationale for phase II trial

Mothers of preterm infants are at a higher risk of a decline in milk production. It has been recommended that they should be evaluated no later than two weeks postpartum to determine what intervention may be required to assist them in augmenting and maintaining an adequate supply of milk
[24]. Although other measures can and should be considered, the use of a galactogogue often becomes the measure of choice, particularly when the other techniques are unsuccessful. The limited body of research on domperidone suggests that it has potential as a galactogogue in mothers of preterm infants; this has led to widespread use of this medication. However, there is a paucity of research to best guide clinicians as to the optimal dose, timing of administration and duration of treatment and to reaffirm safety. EMPOWER was initiated to firmly establish the safety of domperidone for mothers of preterm infants but also guide clinicians regarding initiation, timing and duration of treatment.

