## Methods/design

### Primary research question

The primary research question is: in mothers of preterm infants 23–29 completed weeks (23 1/7-29 6/7 weeks) gestation at birth who are pumping to provide expressed breast milk for their infant(s) and are identified as having an inadequate milk supply, does the administration of domperidone compare to placebo increase breast milk volume without any signs of harm over a 2 week period?

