### Exclusion criteria

i. history of known or suspected cardiac dysrhythmias (tachyarrhythmia, Q-Tc prolongation) or currently on an anti-arrhythmic medication

ii. currently experiencing mastitis

iii. previous breast surgery, including augmentation or reduction, nipple piercing

iv. known chronic or debilitating illness, known abnormal liver function, gastric abnormalities (gastrointestinal hemorrhage, blockage or currently treated acid reflux), HIV

v. known to a have prolactin-releasing pituitary tumor

vi. receiving medications known to alter the metabolism and pharmacokinetics of domperidone (eg. oral “azole” antifungals, erythromycin antibiotics, MAO inhibitors) or medications that have dopaminergic or antidopaminergic activity or affect prolactin levels

vii. mother of higher order pregnancies (triplet, or more)

viii. current cigarette smoking (cigarette smoking is known to diminish prolactin levels)

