### Study outcomes

#### Primary outcome

The primary outcome is the difference between the two groups in achieving a 50% increase in breast milk volume at the end of the first 2-week period (mean day 14 volume- mean day 0 volume at entry).

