Use of supplementation, rates of breastfeeding, and adverse events will be assessed using a chi-square analysis comparing groups.

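### The stated aim of firmly establishing safety goes beyond what 280 mothers per arm, 14 placebo-controlled days and a chi-square test can show for uncommon events

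*Protocol article*

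**What the plan says.** - **Purpose.** The section Rationale for phase II trial states that "EMPOWER was initiated to firmly establish the safety of domperidone for mothers of preterm infants".
- **Primary question.** The Primary research question asks whether domperidone, compared with placebo, will "increase breast milk volume without any signs of harm over a 2 week period".
- **Primary outcome.** It contains efficacy only: "The primary outcome is the difference between the two groups in achieving a 50% increase in breast milk volume at the end of the first" two weeks.
- **Sample size.** The Abstract (Methods/design) derives 488 mothers from 40% vs 28% on that outcome, raised to 560 (280 per group) for 15% dropout. No adverse event rate or harm margin enters.
- **Controlled period.** Under Design, Group B receives "identical placebo 10 mg orally three times daily for 14 days followed by domperidone 10 mg orally three times daily for 14 days". From day 15 both groups take domperidone.
- **Population.** Exclusion criterion i removes mothers with a "history of known or suspected cardiac dysrhythmias (tachyarrhythmia, Q-Tc prolongation) or currently on an anti-arrhythmic medication".
- **Adverse events.** They are item vii, the last of the Secondary outcomes, with gastrointestinal and cardiac events singled out. The Statistical analysis section says that "adverse events will be assessed using a chi-square analysis comparing groups".
- **Oversight.** The Data Safety Monitoring Board (DSMB) reviews adverse events after every 100 recruits (Ethics, informed consent and safety). Duration of study period lists ECG-based reasons for ending study medication.

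**The concern.** Safety is a stated purpose of the trial, and absence of harm is part of its primary question. The only between-group analysis named for it is a test for a difference. Such a test can reveal harm when harm is frequent and large. It cannot support a conclusion of no harm, because a non-significant result is also what one expects when events are few. The article itself singles out cardiac events, where low counts are a real possibility.

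The Rationale describes the drug as already widely used, and the Abstract says that the results will inform mothers and clinicians. If the safety aim stays as worded, a sparse and inconclusive comparison could be taken as reassurance.

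**Working it through.** **1. The plan's own figure.** Inputs from the Abstract: 40% vs 28%, 80% power, alpha 0.05. Sidedness is not stated; two-sided is assumed.

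n per arm = [1.960·√(2·0.34·0.66) + 0.842·√(0.40·0.60 + 0.28·0.72)]² / 0.12² = (1.313 + 0.559)² / 0.0144 ≈ 243.4, so 244 per arm and 488 in total.

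This matches the article. Then 488 × 1.15 = 561, close to the stated 560. With 15% dropout, 560 × 0.85 = 476 remain, or 238 per arm. The efficacy sizing is not in question.

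**2. Power of the adverse event comparison.** The article gives no adverse event rates, so all rates below are assumptions, shown from rare to common. Power is from exact enumeration of two binomial distributions, counting uncorrected Pearson chi-square values above 3.84 (two-sided 5%).

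| Placebo vs domperidone | 280 per arm | 238 per arm |
|---|---|---|
| 0.1% vs 0.2% | 0.2% | 0.1% |
| 0.5% vs 1% | 8% | 7% |
| 1% vs 2% | 15% | 13% |
| 1% vs 3% | 40% | 33% |
| 1% vs 5% | 84% | 77% |
| 5% vs 10% | 62% | 55% |
| 10% vs 20% | 92% | 87% |

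By the formula of step 1, 80% power for 1% vs 2% would need 2,319 mothers per arm.

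**3. The chi-square test with sparse counts.** Take 4 events on domperidone and 0 on placebo, 280 per arm. The statistic is 560 × 4 / 556 = 4.03, above 3.84 and so nominally significant. The expected count is only 2 events per arm, and Fisher's exact test gives p = 0.12. With no placebo events, Fisher's test needs 6 events on domperidone (p = 0.030); 5 give p = 0.061. The named test is thus unreliable for sparse counts, and an exact test has still less power: 8% for 1% vs 2% and 28% for 1% vs 3% at 280 per arm.

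**4. What zero events would exclude.** The one-sided 95% upper limit is 1 − 0.05^(1/n). This is a single-group rate, so the denominator matters.

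| Mothers exposed to domperidone | n | Upper limit |
|---|---|---|
| Group A, as randomized | 280 | 1.06% |
| Group A, after 15% dropout | 238 | 1.25% |
| Both groups, either period | 560 | 0.53% |
| Both groups, after 15% dropout | 476 | 0.63% |

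The pooled rows mix 28 days of exposure (Group A) with 14 (Group B) and carry no placebo comparison.

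Conversely, the chance of seeing no event in 280 mothers is (1 − p)^280: 76% if the true rate is 0.1%, 25% at 0.5%, 6% at 1%.

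**The case against.** **The strong wording sits in one place.** The harm clause in the Primary research question is a question, limited to two weeks, which matches the placebo-controlled window. Elsewhere the aim is milder: the Discussion only hopes to determine safety, and the Rationale also speaks of reaffirming it. This stands as mitigation. The sentence in the Rationale is still a plain statement of purpose, and the harm part of the primary question has no analysis that could answer it.

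**No one says that a null test means safe.** A reader might infer that the investigators will treat a non-significant chi-square as proof of safety. The article does not say so, and the point does not depend on it. What it shows is that the named test could not support the stated aim.

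**The trial does have safety rules.** DSMB reviews and the ECG-based reasons for stopping medication are prespecified. They protect participants but do not add power to the comparison.

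**Common events are covered.** A reader might infer that the trial can say nothing about safety. The article does not support that: at 280 per arm, 10% vs 20% has 92% power, and gastrointestinal events are among those of interest. The frequency of ECG-defined events is not given either. The limit applies to uncommon events.

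**Screening.** It would be too strong to call the mothers cardiac-screened. Exclusion is by history, suspicion or current medication; no baseline ECG is described.

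**Detail may be in the full protocol or analysis plan.** Intervals and interpretation rules could well be there, and their absence from an article is no fault. But the objective and the test are stated here, and no later detail can make this sample establish safety for uncommon events.

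**Conclusion.** The stated safety aim exceeds what the design can deliver for uncommon events. With 280 mothers per arm, a doubling from 1% to 2% would be detected about 15% of the time and a tripling to 3% about 40%; with 238 per arm, 13% and 33%. Large differences in common events are within reach. These figures rest on assumed event rates and a two-sided 5% level for adverse events. The conclusion does not depend on one particular rate: in the range shown, a doubling is poorly detected at placebo rates of 1% or less.

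This is a point about the wording of an objective and the choice of analysis. The efficacy sample size stands, and no larger trial is called for.

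**What to change.** 1. Reword the safety aim in the Rationale and the Primary research question: estimate 14-day adverse event rates versus placebo in mothers without known or suspected dysrhythmia.
2. In the Statistical analysis section, replace the chi-square test for adverse events with the risk difference and an exact or score 95% confidence interval. If a test is wanted, use an exact one.
3. Name days 0–14 as the only placebo-controlled safety comparison, and report days 15–28 as uncontrolled exposure.
4. State that a non-significant difference will not be read as evidence of no harm.
5. If a zero-event limit is quoted, name its denominator: 1.06% for 280 Group A mothers (1.25% for 238), or 0.53% for all 560 exposed in either period (0.63% for 476).

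The cost is a change of wording and of one analysis, with no extra patients or procedures. The downside is a more modest safety claim.
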